#### Secondary objective

The secondary objective is to assess the effectiveness of Beat the Kick in reducing substance use. This will be measured by comparing changes in substance abuse from pre-treatment to follow-up between the experimental and CAU groups. The hypothesis is that participants in the experimental group will show a greater reduction in substance use compared to those in CAU at follow-up.

### Trial design {8}

This multicenter, parallel-group superiority randomized controlled trial employs a Zelen design to evaluate the effectiveness of the Beat the Kick intervention in enhancing autonomous motivation and reducing substance use among adults with MID. The Zelen design ensures unbiased group assignment by randomizing 138 consecutive participants into two groups—treatment and CAU—prior to obtaining informed consent, thereby minimizing selection bias and mirroring real-world clinical scenarios [23]. Participants are allocated in a 1:1 ratio, with 69 individuals in each group.

Randomization occurs at the individual level, which introduces the potential risk of carry-over effects if therapists treat participants in both the CAU and Beat the Kick intervention groups. To mitigate this risk, therapists are exclusively assigned to either the intervention or CAU group, ensuring no overlap in their caseloads. Additionally, therapists from the intervention and CAU groups are employed by different organizations and do not collaborate or exchange information during the study period. This separation prevents contamination and enhances the validity of the findings. Following the study, therapists can provide valuable reflections on their experiences with the training, including its perceived effectiveness and practical applicability, offering further contextualization of the outcomes.

Assessments are conducted at four time points: pre-treatment (T1), post-treatment (T2), and follow-up evaluations at 1 month (T3) and 6 months (T4) after the intervention. This schedule allows for the measurement of both immediate and sustained effects of the intervention.

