## Intervention

### Explanation for the choice of comparators {6b}

The comparator in this study is the CAU condition. This choice enables a direct evaluation of the effectiveness of the Beat the Kick intervention relative to the standard care typically provided to people with MID and substance abuse problems. Participants in the CAU group will receive support from their intellectual disability healthcare organization, which may involve a multidisciplinary team including physicians, nurses, psychologists, social workers, and counselors.

Standard care in the CAU group encompasses a wide range of approaches tailored to individual needs. These may involve techniques to enhance readiness for change, as well as strategies focused on building supportive relationships between the individual and their caregiver. The aim is to create a stable and safe environment in which individuals feel valued and engaged in meaningful daily activities that foster a sense of competence and reduce challenging behaviors. Standard care may also include guidance, information, and assistance related to substance use and intellectual disabilities, along with regular check-ups to monitor progress, assess needs, and provide general support. Participants in the CAU group will not receive the structured Beat the Kick intervention. However, they will continue to receive care from their regular healthcare providers, including support related to substance use and intellectual disabilities. This ensures that all participants receive an ethically appropriate level of baseline care while allowing for a valid comparison with the added value of the intervention.

In addition, the use of a CAU comparator rather than a waitlist control helps prevent bias that could arise from nocebo effects. Participants placed on a waitlist may experience demoralization, reduced motivation, or worsening of symptoms due to the absence of support, which can artificially inflate the intervention’s observed effectiveness. By comparing Beat the Kick to the care that is actually available in practice, the study maintains both clinical relevance and methodological integrity.

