### Intervention description {11a}

The Beat the Kick intervention consists of ten weekly individualized sessions, each lasting 45–60 min, designed to help participants understand and change their substance abuse patterns, identify triggers, and adopt healthier coping strategies. The intervention draws upon Self-Determination Theory [26] and Motivational Interviewing [33] to foster autonomous motivation. It does so by supporting the basic psychological needs of autonomy, competence, and relatedness, and by creating a safe, supportive environment in which participants are encouraged to explore and commit to meaningful behavior change.

Each participant is guided by a healthcare professional who has completed the “Train the Trainers: Beat the Kick” program. The program begins with an introductory session in which the trainer builds rapport, discusses expectations, and tailors the intervention to the participant’s specific needs and circumstances. To prevent potential carry-over effects, staff members supporting participants in the intervention group will not simultaneously support participants in the CAU group. This separation ensures that intervention-specific knowledge and techniques are not inadvertently applied in the control condition, preserving the integrity of the comparison.

Subsequent sessions are structured thematically. The second and third sessions help participants explore their substance use behaviors and attitudes through interactive activities such as online assignments, video clips, and discussions. Concepts like the distinction between substance addiction and substance abuse are clarified with visual aids. In sessions four through six, cognitive-behavioral techniques are introduced using the ABC model [34], which links triggers, beliefs, and behaviors. These sessions focus on identifying craving triggers and developing healthier responses.

Session seven emphasizes identifying personal values and interests to explore alternative activities that can replace substance use, while session eight focuses on evaluating the participant’s social network and identifying individuals who can offer support during challenging moments. The final two sessions consolidate the learnings by developing a personalized action plan and discussing options for ongoing support. The program concludes with a certificate recognizing participants’ efforts.

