Before the intervention starts, participants’ regular support staff attend a 1.5-h clinical briefing session delivered by the trainer. This session is designed to improve staff members’ understanding of substance use and the intervention content, enhancing their ability to support participants appropriately. Additionally, a helper from the participant’s own social network provides ongoing support throughout the intervention period, offering a trusted and accessible source of encouragement and reflection.

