### Recruitment {15}

Participants will be selected from the caseloads of six organizations affiliated with the Academic Collaborative Center Living with an intellectual disability (AWVB) at Tranzo, Tilburg University. Eligible individuals with MID who are not currently receiving substance abuse treatment will be identified through a random selection process carried out by the principal researcher. From this pool, 138 people with MID meeting the inclusion and exclusion criteria will be pre-assigned to either the experimental or control group using a Zelen design. The randomization process will be conducted by the principal researcher in an independent capacity to ensure objectivity and minimize bias. The intervention will be delivered by behavioral specialists from the six participating healthcare organizations to ensure standardized implementation across all sites.

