## Assignment of interventions: allocation

### Sequence generation {16a}

The study uses a Zelen pre-randomization design. Participants are individually randomized 1:1 to Beat the Kick or care-as-usual (CAU) using a centralized, computer-generated sequence with permuted blocks of variable size, stratified by addiction type (alcohol vs. cannabis/other drugs) to maintain balance across strata. Randomization is not clustered; clients from the same team may be allocated to either arm.

To minimize provider contamination while preserving individual randomization, trainers are assigned exclusively to a single arm (intervention or CAU) and do not deliver care in the other arm during the trial. Trainer and site identifiers are recorded at allocation; trainer will be modeled as a random effect in mixed-effects analyses to account for provider-level clustering. Any unavoidable cross-coverage will be documented a priori and examined in sensitivity analyses.

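### The claim that the two arms' therapists come from different organisations contradicts the protocol's own recruitment, comparator and randomisation sections, so the stated safeguard against contamination is not established

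*Protocol article*

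**What the plan says.** **Who employs the therapists.** Trial design {8} states that "therapists from the intervention and CAU groups are employed by different organizations and do not collaborate or exchange information during the study period", and presents this as what keeps the arms from contaminating each other.

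**Who delivers the intervention.** Recruitment {15}: "The intervention will be delivered by behavioral specialists from the six participating healthcare organizations to ensure standardized implementation across all sites".

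**Who delivers usual care.** Explanation for the choice of comparators {6b}: "Participants in the CAU group will receive support from their intellectual disability healthcare organization". Clients are recruited from the same six organisations (Study setting {9}, Recruitment {15}).

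**How clients are allocated.** Sequence generation {16a}: "Randomization is not clustered; clients from the same team may be allocated to either arm". Stratification is by addiction type only. Trainers work in one arm, which may be either arm. Site is recorded. Unavoidable cross-coverage is to be documented and examined in sensitivity analyses.

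**Support staff.** Intervention description {11a} promises that "staff members supporting participants in the intervention group will not simultaneously support participants in the CAU group", and Methods for additional analyses {20b} repeats the promise, with monitoring and control in the analysis where overlap cannot be avoided. Section {11a} also says that, before the programme starts, participants' "regular support staff attend a 1.5-h clinical briefing session delivered by the trainer".

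**The model.** Statistical methods {20a} names group, time, their interaction, addiction type, baseline outcome, living arrangement and prior treatment, with participant and trainer random effects. It names no organisation term. It also says that trainers are assigned only to the intervention group, whereas {16a} has trainers in either arm.

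**The concern.** The protocol rests its protection against contamination on a staffing arrangement that its other sections contradict. A reader cannot tell which trial is being run, and the two possibilities carry different risks.

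- If the arms' therapists really have different employers, the comparison is between Beat the Kick given by staff of some organisations and usual care given by staff of others. Individual randomisation balances the clients, not the providers. A systematic difference between employers would be part of the estimated effect.
- If both arms run inside each organisation, the employer problem disappears, and so does the safeguard. Protection then depends on arm-exclusive trainers and on the promised separation of support staff. That separation is hard to keep where one team has clients in both arms and its regular staff are briefed on the intervention. The likely direction is dilution of the difference.

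The meaning of the trainer random effect also depends on the answer, because {16a} and {20a} disagree on whether the usual-care arm has trainers at all.

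**Working it through.** **1. Can the statements be reconciled?**

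- Recruitment {15}: all six organisations supply Beat the Kick trainers.
- Comparators {6b} with Recruitment {15}: usual care comes from the client's own organisation, which is one of the same six.
- Together: any organisation with at least one usual-care client has staff in both arms. Trial design {8} says that this does not happen.

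One way out is that some of the six supply no trainers, which contradicts {15}. The other is that some hold no usual-care clients. Allocation is individual and 1:1, without regard to organisation. With equal shares (assumed), 138/6 = 23 clients per organisation. Treating allocations as independent, the chance that a given organisation has no usual-care client is 0.5^23 ≈ 1.2 × 10⁻⁷. Neither way out works.

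**2. Support staff.** Under {16a}, clients of one team may fall in either arm. Under {11a}, the regular support staff of intervention participants are briefed. Where a team does hold both arms, keeping the promise in {11a} and {20b} would require dividing the team's staff by arm. The protocol does not say how. Arm-exclusive trainers do not achieve it, because trainers and regular support staff are different people.

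**3. The plan's own figure.** Inputs from Sample size {14}: f = 0.25, four measurements, correlation 0.5, two groups, two-sided 5%. The noncentrality is f²·N·4/(1 + 3 × 0.5) = 0.0625 × 4 × N/2.5 = 0.1·N, with 1 and N − 2 degrees of freedom. Power is 0.798 at N = 80 and 0.808 at N = 82, so 82 reproduces. With 40% dropout, 82/0.6 = 136.7, so 137, or 138 for equal arms. No sample-size figure is wrong on this point.

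**4. Illustration of the Trial design {8} reading only.** Assumptions not in the protocol: three organisations per arm, equal sizes, the ICC values, and no allowance for the trainer random effect. Design effect DE = 1 + (m − 1)·ICC; type I error when organisation is ignored = 2·(1 − Φ(1.96/√DE)). With 82 completers, m = 82/6 = 13.7.

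| Assumed ICC | DE | Type I error |
|---|---|---|
| 0.01 | 1.13 | 6.5% |
| 0.05 | 1.63 | 12.5% |
| 0.10 | 2.27 | 19.3% |

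With all 138 analysed (m = 23, no dropout), the design effects are 1.22, 2.10 and 3.20 and the error rates 7.6%, 17.6% and 27.3%.

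**5. Illustration of the within-organisation reading.** f = 0.25 with two groups is d = 2 × 0.25 = 0.5. If 20% of usual-care clients received the full effect (assumed), the observed difference would be 0.5 × (1 − 0.20) = 0.40.

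**The case against.** **Overlap is acknowledged.** One might infer that contamination has been overlooked. It has not: {16a} promises documentation and sensitivity analyses, and {20b} promises monitoring and control in the analysis. This stands. What remains is that both treat overlap as an exception, while the allocation rule allows shared teams as a matter of course, and neither names the exposure to be recorded.

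**Arm is not shown to be inseparable from organisation.** The sentence in {8} concerns therapists' employers. Clients are individually randomised, so their home organisation is not tied to arm. Some difference in providers is also inherent in comparing a trainer-led programme with usual care. This stands, so the confounding argument is limited to the therapist's employer.

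**A missing organisation term does not bias the comparison.** With both arms in each organisation, omitting it costs precision and ignores site differences; it does not bias the randomised contrast. Baseline outcome and the participant and trainer random effects already take up part of the variation. This stands.

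**Shared staff are possible, not established.** It is tempting to say that briefed staff will also support usual-care clients. The text says only that same-team clients may be in either arm, and it commits to separation.

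**The numbers are soft.** The three-versus-three split conflicts with {15}, the ICCs are chosen, and the calculation ignores the trainer random effect. Full-effect exposure in 20% of usual-care clients is a strong assumption when the route is a 1.5-hour staff briefing set against ten individual sessions. All of this stands.

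None of it removes the contradiction. A statistical analysis plan could add a site term, but it could not make the staffing statements agree.

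**Conclusion.** The contradiction is real. The different-employers statement in {8} cannot hold together with {15}, {6b} and {16a}, and {20a} conflicts with {16a} on which arm has trainers. The safeguard that the protocol relies on is therefore not established.

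If {8} were true, arm would be tied to the therapist's employer, and neither an organisation term nor the trainer random effect could separate them. If {15} and {16a} are true, the safeguard does not exist as described, and some dilution is possible.

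The documents do not allow either consequence to be sized. The type I error range of about 6.5% to 19.3% at 82 completers applies only to the {8} reading, under an assumed split and assumed ICCs. It is not an estimate for this trial. The fall from 0.50 to 0.40 is likewise an assumption.

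A reader might infer that the trial's effect is confounded with organisation, or that its error rate is already inflated. The protocol does not support either statement. It leaves the delivery arrangement unsettled.

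**What to change.** 1. **Settle the facts first.** Establish which organisations staff which arm, then make {8}, {11a}, {15}, {16a}, {20a} and {20b} agree, including whether the usual-care arm has trainers. If both arms run within each organisation, remove the different-organisations sentence from {8} and the claim that this separation prevents contamination. Cost: a text correction.

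2. **Add organisation as a fixed effect** (six levels) to the primary and secondary models. Its purpose is precision and allowance for site differences, not removal of bias. Cost: 6 − 1 = 5 degrees of freedom; site is already recorded. Stratifying by organisation is optional.

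3. **Log exposure prospectively.** For every usual-care client, record whether any of their support staff attended a briefing or support an intervention client. This cannot be recovered reliably at analysis. Cost: a short record per client and no extra staff.

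4. **Use the log in the sensitivity analysis promised in {16a}**, keeping intention-to-treat as primary. Do not rely on dropping exposed usual-care clients: that is a post-randomisation exclusion in one arm only and can itself introduce selection bias.

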## Methods

### Study setting {9}

This multicenter study will be conducted in six healthcare organizations for people with intellectual disabilities in the Netherlands, all partners of the Academic Collaborative Center Living with an intellectual disability (Tranzo, Tilburg University). Each participating organization cares for approximately 20 adults per year with co-occurring MID/BIF and hazardous substance use who match our eligibility profile. To secure a sufficient recruitment pool and geographic spread, six organizations are included (combined projected pool ≈120/year), supporting the feasibility of recruiting *N* = 138 within the planned accrual period. The organizations are distributed across urban and rural regions, providing a heterogeneous and therefore representative sample of adults with MID in Dutch intellectual disability services (Fig. 1).

**Fig. 1 Fig1:**
[figure not shown]
Gantt chart

### Eligibility criteria {10}

#### Inclusion criteria

Participants are eligible if they meet the following criteria:MID or BIF: Defined by an IQ of 50–70 (MID) or 70–85 (BIF) combined with severe adaptive functioning limitations (defined by significant impairments in at least two of the following domains: conceptual, social, and practical skills, as outlined in the DSM-5). Both groups are collectively referred to as “individuals with MID,” reflecting their shared characteristics and support needs. In the Netherlands, these groups qualify for specialized mental health care and are often grouped in research, practice, and policy contexts [5].Substance abuse: Hazardous alcohol or drug use that negatively impacts physical, psychological, interpersonal, or social well-being for a duration of at least 12 months [10]. To focus the intervention on individuals with problematic substance abuse rather than severe substance use disorders, participants with indications of high-intensity or clinically complex use patterns will be excluded. This will be assessed using the Substance Use and Misuse in Intellectual Disability Questionnaire [24], which includes the Alcohol Use Disorders Identification Test (AUDIT) and the Drug Use Disorders Identification Test (DUDIT) to screen for substance abuse severity. Participants who exceed the established clinical thresholds for high-risk use (AUDIT > 19 or DUDIT > 24) will not be eligible to participate, as their level of use suggests the need for more intensive, specialized addiction care [24, 25].Lack of autonomous motivation: Participants must exhibit low autonomous motivation to change their substance use, as this is the primary target of the intervention. Autonomous motivation will be measured using the Treatment Self-Regulation Questionnaire (TSRQ) [21], which assesses the extent to which individuals engage in change based on personal value, interest, or internal goals [26]. This criterion ensures that the intervention is tested in individuals who are not yet ready or internally motivated to change, in line with the study’s aims.Age: Participants must be 18 years or older to ensure legal competence for informed consent and appropriateness of intervention content.Language proficiency: Participants must have sufficient Dutch language proficiency (minimum B1 level) to understand the intervention content, complete study measures, and engage in therapeutic conversations. This ensures the validity of assessments and meaningful participation.

#### Exclusion criteria

Participants will be excluded if any of the following apply:Medication-related substance use: Individuals whose substance use is exclusively related to prescribed medications with potential for misuse (e.g., opioids, benzodiazepines, or ADHD medications like methylphenidate) will be excluded. This distinction is made in order to focus the intervention on non-medical substance misuse and to avoid medical confounds [2].Lack of response or confusion: Individuals who are unable to provide meaningful verbal or non-verbal responses or who display significant confusion will be excluded. This ensures participants can engage with intervention content and assessments in a reliable and ethical manner.Concurrent or planned substance use treatment: Individuals currently receiving, or planning to begin, other substance use interventions during the study period will be excluded to prevent treatment contamination and ensure internal validity of outcomes [27, 28].Unstable living situation: Homelessness or unstable housing will be grounds for exclusion due to the increased risk of dropout, relapse, and inability to guarantee follow-up. Stable living conditions are a known prerequisite for effective outpatient interventions (29, 30]).Pregnancy: Pregnant individuals will be excluded due to ethical concerns and potential medical complications related to withdrawal, stress, and fetal risk [31].Inability to give informed consent: Individuals who are legally restricted from consenting or who demonstrate cognitive impairments beyond the MID/BIF range will be excluded. However, when applicable, legal representatives may provide consent on their behalf in accordance with ethical guidelines, allowing participation when appropriate [32]. This ensures ethical standards are upheld while maximizing inclusion.

